## Abstract

**Background:**

Approximately 10–20 % of adults with intellectual disabilities engage in challenging behaviours such as aggression, destructiveness, and self-injury, which are often accompanied by feelings of anger. The inability to manage anger can reduce quality of life. For example, aggression is a strong predictor of out-of-area placements and is a risk variable for abuse. Recent research suggests that mindfulness-based therapies (specifically, Singh’s Soles of the Feet meditation) can help people with intellectual disabilities manage angry emotions, with resultant reductions in challenging behaviour. However, previous research has been single-case design studies, and no group studies have been published with people with intellectual disabilities and aggressive behaviour.

**Methods/design:**

For this feasibility study, a UK protocol will be developed for use by health professionals within National Health Service (NHS) Intellectual Disability (ID) teams, based upon Singh’s Soles of the Feet manual. Twenty adults with intellectual disabilities and identified problems with anger control will be recruited and six sessions will be delivered by a trained ID clinician. The study will monitor participant’s aggressive behaviour, health-related quality of life, anxiety, depression, and use of support services (medication, hospital appointments etc.). These will be measured at three time points: (1) Baseline (within 2 weeks prior to the first session of the intervention), (2) 2 months post-baseline, and (3) 6 months post-baseline. Qualitative interviews will be conducted with participants, their carers, and the therapists who delivered the intervention. In order to help design an economic evaluation alongside a future full trial, we will cost the intervention and test the acceptability and validity of health economics measures to record resource use and health-related quality of life outcomes.

**Discussion:**

The data from this study will inform the feasibility of the project protocol and intervention, which will help develop future research and to determine whether a larger, randomised controlled trial with concurrent economic evaluation is feasible.

**Trial registration:**

UKCERN: 16743.

## Background

In the UK, 2 % of adults and 3.5 % of children have an intellectual disability (ID) [1, 2]—defined as an IQ below 70, alongside adaptive behaviour deficits, and onset within childhood. Approximately 10–20 % of people with ID engage in challenging behaviour [3–7], and challenging behaviours are likely to persist over extended periods of time [8]. Severe challenging behaviour has a range of negative impacts, such as a lower quality of life, a negative impact on carer well-being [9, 10], reduced access to community services, and admission to intensive and specialist, and therefore costly, residential, or forensic services [11].

When interviewed, some adults with ID report that they find their own anger and challenging behaviour difficult to cope with and aversive and described feeling regretful after engaging in challenging behaviour [12–14]. Qualitative studies and a recent meta-synthesis have found that adults with ID are keen to learn how to self-manage anger [15].

Leading researchers on anger have called for creative and more effective interventions than the most common treatment methods such as cognitive behavioural therapy (CBT). CBT holds particular challenges for people with ID, as it requires high levels of language skills, and the ability to be introspective and self-aware, and yet does not explicitly address the development of such awareness [16].

There is an ongoing debate in the field about how best to define the complex construct of mindfulness (see [17]). An oft-cited definition of mindfulness is ‘paying attention in a particular way, on purpose, in the present moment and non-judgementally ([18]. p.4)’. Mindfulness-Based Stress Reduction (MBSR) was originally developed in the late 1970s, and MBSR courses today closely follow the original format. MBSR courses are taught in groups, for around 2.5 h a week for 8 weeks, with a full day of silent meditation practice around the sixth week. Participants are given home practices of around 45 min to an hour each day [18].

Mindfulness has the potential to address a number of psychological processes and states that are relevant to the risk of anger and resultant challenging behaviour [16].

These include reduced emotional reactivity to a trigger by observing anger-related sensations in the body without attempting to avoid or act on them. Evidence suggests that mindfulness is particularly relevant to the reduction of negative emotional episodes [19] because rumination increases the emotion of anger [20]. Conversely, a non-judgemental view of one’s thoughts may help reduce the negative impact of ruminative patterns. The ability to self-monitor one’s own mood states is regarded as being central to anger regulation. To adjust an individual’s anger response, there needs to be an awareness that anger is present. Aggressive outbursts may become autotomized anger responses, with little awareness of conscious attention (for people both with and without ID). Mindfulness training enables awareness of the bodily, cognitive, and behavioural signs of anger and opens the possibility of autotomizing non-aggressive responses [16].

Mindfulness-based interventions (MBIs) are recommended by the National Institute for Health and Care Excellence (NICE) in the UK. Specifically, mindfulness-based cognitive therapy (MBCT) is recommended for recurrent depression [21], and Dialectical Behaviour Therapy for Borderline Personality Disorder [22]. Typical MBIs rely on complex language to reflect on the experience of meditation, which may be cognitively demanding for individuals with ID. Therefore, it is important to consider how to adjust approaches for this population. In the USA, Soles of the Feet (SoF) meditation has been developed as a way of making MBIs accessible for people with ID [23]. It has been successfully used in ID populations to self-manage anger and, at long-term follow-up, has resulted in reported reductions or total elimination of aggressive behaviours [24–28]. It has also been used to help reduce deviant sexual arousal [29], smoking [30], and health behaviours contributing to obesity [31].

A recent systematic review [32] found the most frequent objective of MBIs for individuals with ID was the reduction of aggressive behaviour (explored in 7/12 studies), and of these, all reported a reduction in aggressive behaviour. Although there were 12 studies in the Hwang and Kearney review, this represents just 22 participants as they were all single-case design studies.

The Singh SoF manual [23] was originally designed to help individuals with ID cope with anger and reduce aggressive behaviour [25]. Individuals are taught to recognise situations that are ‘triggers’ for their anger, then guided through the steps of the SoF meditation. These include breathing naturally without trying to respond to angry thoughts or emotions and then shifting attention to, and being mindful of, the soles of their feet (a neutral part of the body). This technique is tailored to the cognitive level of the individual and enables the regulation of emotional states and behaviours. Thus, it is a good match with current philosophical and policy perspectives on empowering the lives of people with ID [32–34].

Hwang and Kearney [32] noted that teaching SoF to people with ID (in the studies, they reviewed) was labour-intensive, which creates a problem with intervention accessibility for patients and providers alike. The authors called for group evaluation: “Diversifying intervention methods and research methodology is the key” (p. 325). The proposed study addresses both the issue of labour intensity and of group evaluation. First, we aim to develop an adapted SoF package: Using Mindfulness for Anger and Aggressive Behaviour with people with Learning Disabilities—Soles of the Feet (henceforth referred to as UMAA-LD SoF), that is delivered over six sessions by health professionals working in the UK National Health Service (NHS). This serves to create an intervention that is comparable or shorter in timescale to other developed clinical interventions for anger and aggressive behaviour in this population [35–38]. Second, we are utilising a group design and so taking a step up the ‘evidence hierarchy’ from the single-case designs used thus far with SoF with people with ID and aggressive behaviour. Third, it is important that researchers are able to measure levels of mindfulness within a population where intervention studies are being conducted. Existing measures of mindfulness such as the Five Facet Mindfulness Questionnaire [39] are likely to be too cognitively demanding for people with ID. Therefore, development and validation of a measure of mindfulness for this population will be undertaken as part of the UMAA-LD study.

Few studies evaluating MBIs consider the costs along with the possible clinical benefits [40]. In the original SoF evaluation [28], a benefit-cost analysis indicated significant cost savings following SoF delivery due to a reduction in staff absenteeism at work. The SoF intervention costs were not included in the analysis as they were absorbed into routine behaviour training costs. These savings may not be representative of the costs of delivery within a UK health care setting. In order to evaluate whether SoF is a cost-effective intervention, a full economic evaluation alongside a randomised controlled trial is necessary. We chose to conduct a feasibility study because we wanted to explore the practicality of the proposed intervention and methodology. Therefore, this feasibility study will contribute to the growing evidence base of using SoF for people with ID and anger and aggressive behaviour.

### Aims

The principal aims of this feasibility study areTo test the UMAA-LD SoF protocol and research process including delivery across a NHS site, referral pathways, number of eligible participants and carers, treatment fidelity, willingness of clinicians to recruit, questionnaire completion rates, the time taken to complete outcome and process measures, and acceptability and accessibility of the UMAA-LD SoF protocolTo develop and carry out a preliminary test of the reliability and validity of a Mindful Awareness for adults with an Intellectual Disability Scale (MAIDS)To cost the UMAA-LD SoF intervention and evaluate the acceptability and validity of the health economic outcomes for a subsequent full economic evaluationTo develop and test the feasibility of a protocol for a full-scale effectiveness randomised control trial (RCT) with concurrent economic evaluation of the UMAA-LD SoF intervention

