## Methods

### Design

A single-arm study with 20 participants at three time points of measurement: baseline, immediately after intervention (2 months post-baseline), and follow-up (6 months post-baseline). A sample size of 20 is feasible and economical whilst providing sufficiently precise estimates of variances for powering larger studies. The UMAA-LD SoF intervention will take place over six sessions, at a rate of one session per week.

A researcher will visit participants at all three time points to assist with completion of outcome measures. This will take place either in the participant’s home or a place of their choice (e.g. their local clinic).

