#### Qualitative interviews

Qualitative semi-structured one-to-one interviews with participants and carers will be conducted after all outcome data have been collected (6 months after baseline) focusing on the interview topics described below.
*Participants:* How accessible/acceptable SoF meditation was, the impact upon their feelings and expressions of anger, their quality of life, adherence and perceived barriers to the intervention, use of the mindfulness practice audiofiles at home, whether they will continue to use SoF meditation, exploration of any relationship changes with their carer, and any future support needed.
*Carers:* Perceived impact of the intervention on their offspring/client, their relationship with their client/ family member throughout the intervention, and exploring what, if any, impact it had on their own lives, both personally and as a carer.
*UMAA-LD SoF therapists:* their experiences of mindfulness prior to training, their experience of being trained to use UMAA-LD SoF, experiences of delivering the UMAA-LD SoF, including the accessibility of the manual for themselves and clients and the perceived effects on participants and carers.

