#### Protocol for a full-scale effectiveness trial

To address aim 4, a full study would be considered feasible if (1) recruitment rate found was more than 50 %, (2) if the retention rate found was more than 50 % at final follow-up, and (3) if adherence rate was greater than 50 % for the completing participants.

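### Aim 4 is to test the feasibility of an RCT, but the three progression rates come from a single-arm study and do not by themselves show that randomisation or a control arm would be acceptable

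*Protocol article*

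**What the plan says.** Under Aims, the fourth aim is to "develop and test the feasibility of a protocol for a full-scale effectiveness randomised control trial (RCT"). The Discussion paragraph of the abstract gives the same purpose: "to determine whether a larger, randomised controlled trial with concurrent economic evaluation is feasible".

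Under Design, the study is "A single-arm study with 20 participants at three time points of measurement". The reason given for its size is that "A sample size of 20 is feasible and economical whilst providing sufficiently precise estimates of variances for powering larger studies".

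The section Protocol for a full-scale effectiveness trial is expressly tied to aim 4. It sets three conditions: "a full study would be considered feasible if (1) recruitment rate found was more than 50" %; "if the retention rate found was more than 50 % at final follow-up"; and adherence above 50% among those who complete.

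Under Qualitative interviews, the participant topics begin with "How accessible/acceptable SoF meditation was" and go on to impact, adherence, barriers to the intervention and future support. Carers are asked about impact and relationships. Therapists are asked about training and delivery.

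**The concern.** An RCT asks people to accept allocation by chance and asks some of them to be followed up without the intervention, at least for a time. The study asks for neither. Its recruitment rate describes uptake of a certain offer, and its retention rate describes people who were offered the treatment.

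The rule nevertheless moves directly from these rates to the conclusion that a full study is feasible. If all three pass, the authors could report aim 4 as met although the feature that separates an RCT from this study was not examined. The article itself gives a reason why this could matter. Its Discussion expects direct benefit to participants in an area with few available treatments, so certainty of receiving the treatment is a plausible motive for joining.

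**Working it through.** **Stated figures.** The document's figures here are the sample size of 20 and the 50% thresholds. Neither is derived, so there is nothing to reproduce. The size is justified by the precision of variances, and the point does not depend on it.

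**What an RCT needs, set against what the article lists.**

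| Element of RCT feasibility | Where the article covers it |
|---|---|
| Referral pathways, eligible numbers, clinicians' willingness to recruit | Aims (aim 1) |
| Screening and recruitment rates, drop-out and reasons, questionnaire completion, fidelity, home practice | Feasibility process measures |
| Means and variances for a power calculation | Method of analysis |
| Costing and suitability of economic measures | Health economic evaluation |
| Acceptability of the intervention | Qualitative interviews |
| Acceptability of chance allocation to participants, carers or clinicians | Not among the listed measures, topics or criteria |
| Retention without the intervention | Cannot be observed in a single-arm study |

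The first five rows inform an RCT protocol. The last two are specific to randomisation, and the three criteria do not touch them.

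**Illustration for recruitment.** Let r be the recruitment rate observed here and w the share of those recruits who would also have accepted randomisation. If nobody who declines a certain offer would accept a chance of it, the RCT recruitment rate is r × w. It stays above 50% only if w > 0.50 / r. The document gives no value for w; the range 0.5 to 1.0 is an assumption.

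| Observed r | w = 0.5 | w = 0.6 | w = 0.8 | w = 1.0 | w needed to exceed 50% |
|---|---|---|---|---|---|
| 55% | 27.5% | 33% | 44% | 55% | 0.50/0.55 = 0.91 |
| 60% | 30% | 36% | 48% | 60% | 0.50/0.60 = 0.83 |
| 70% | 35% | 42% | 56% | 70% | 0.50/0.70 = 0.71 |
| 80% | 40% | 48% | 64% | 80% | 0.50/0.80 = 0.63 |

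A result just over the threshold leaves little room. A result well over it tolerates considerable reluctance. The table shows how sensitive the rule is; it is not evidence that w is low.

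**Retention.** No similar calculation is possible, because the direction is not fixed. A control participant may lose interest without treatment. Equally, a control participant is spared six sessions of up to 90 minutes (up to 6 × 90 = 540 minutes), daily home practice and carer attendance, and a waiting list gives a reason to stay.

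**The case against.** The strongest reply has three parts.

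First, the Discussion of the article says that an anger management intervention has already been tested by RCT in people with intellectual disabilities, and that this answers doubts about whether such trials can be done. The authors may therefore have treated randomisation as largely settled and aimed the study at what is new. This carries some weight and softens the gap. But the earlier trial concerned another intervention. It is background, not a test made here, and it is not one of the criteria.

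Second, the programme is staged. The Background gives the purpose as exploring practicality, and the Discussion says an RCT protocol will be developed if results are promising. A single-arm first step is legitimate. That stands, and the design need not change. What remains is that aim 4 and its criteria claim more than those sections do.

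Third, this is a condensed article, and the full topic guide and screening log are not shown. That also stands: a reader might infer that the study records nothing from people who decline, but the article does not say so. The point rests on the criteria that the article itself assigns to aim 4, not on the silence of papers not shown.

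**Conclusion.** The mismatch between aim 4 and its criteria is real and should be corrected. Passing all three thresholds would show that the intervention can be delivered and evaluated in this setting. It would not by itself show that an RCT is feasible.

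Two stronger readings are tempting and not supported. One is that the rates fail to answer aim 4 at all; in fact they inform several parts of an RCT protocol. The other is that they are upper bounds for an RCT. Recruitment to a certain offer may well overstate recruitment to an RCT, but for retention the document fixes no direction.

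The size is unknown. The break-even shares of 0.91 at an observed 55% and 0.63 at 80% rest on an assumed model and on no data from the study.

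**What to change.** (a) Reword aim 4, the matching sentence in the abstract, and the section Protocol for a full-scale effectiveness trial. Possible wording: *Meeting the three criteria will indicate that the intervention can be delivered and evaluated, and will inform the protocol of an RCT. Acceptability of randomisation and retention in a control arm remain to be confirmed, for example in an internal pilot.* The rates should not be described as upper bounds.

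(b) Add one short question to the planned participant, carer and therapist interviews and, where possible, to the researcher's screening visit: would they take part, or support taking part, if allocation to the intervention or to usual care or a waiting list were decided by chance? Report the answers descriptively.

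The limits of (b) should be stated with the results. The answers are hypothetical. Participants and carers are interviewed at six months, after the intervention has been offered. Under Recruitment, the researcher meets only people who return a reply slip, so earlier decliners are not reached. Referring clinicians are reached only where they also act as therapists. The question therefore does not estimate w among all those approached.

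The cost is one extra topic at contacts already planned, any ethics approval needed for it, and a more modest conclusion. Part (a) alone removes the overstatement.

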## Methods

### Design

A single-arm study with 20 participants at three time points of measurement: baseline, immediately after intervention (2 months post-baseline), and follow-up (6 months post-baseline). A sample size of 20 is feasible and economical whilst providing sufficiently precise estimates of variances for powering larger studies. The UMAA-LD SoF intervention will take place over six sessions, at a rate of one session per week.

A researcher will visit participants at all three time points to assist with completion of outcome measures. This will take place either in the participant’s home or a place of their choice (e.g. their local clinic).

### Participants

Twenty participants will be recruited for the study. Inclusion criteria are (1) over the age of 18 years, (2) with an ID (established through the administration of the Wechsler Abbreviated Scale of Intelligence 2nd Edition [41]) and Adaptive Behaviour Assessment System© (ABAS; 2^nd^ Edition [42]), (3) have clinically significant difficulty with anger control as assessed by their clinician, (4) able to give informed consent, and (5) has a family member or paid carer who has supported them for a minimum of 6 months, is available to participate in the treatment sessions, and who currently provides a minimum of 2-h support per week to the participant. Although language ability is not an inclusion criterion, if participants are able to give informed consent, then they are also likely to have the language level needed to participate in an UMAA-LD SoF intervention.

Exclusion criteria are (1) existing diagnosis of autism spectrum disorder (because of potential difficulties with more abstract concepts relating to mindfulness when ID and autism are co-morbid), (2) presence of mental health problems or behaviour that may prevent the participant from interacting with the carer or therapist or retaining information from the therapy (e.g., dementia, active psychosis), and (3) individuals who are currently receiving direct psychological intervention (e.g. relaxation training, DBT, CBT).

### Recruitment

The research team will meet with clinicians working in NHS ID teams prior to commencement and explain the study. If clinicians are willing to be involved in recruitment, they will be given a supply of study information packs, comprising a letter of invitation, a participant information sheet, a carer information sheet, a reply slip, and a Freepost return envelope addressed to the researcher. Clinicians will be required to explain to the person with ID that a follow-up telephone call can be made by the researcher should they agree to this.

If the person with ID agrees to a follow up telephone call, clinicians will contact the potential participant once by telephone to check if they have retained the study information pack. If the pack has been mislaid, the clinician will offer to send a second pack. Adults with ID are often supported by several different carers, working across several settings (e.g. a person’s home environment, day centre). This situation means there is a high likelihood of study packs going missing.

On receipt of reply slips with the name and contact details of the potential participant agreeing to contact by the researcher, the researcher will arrange an initial screening visit so that they can explain verbally to the person with ID and their carer what the study involves and so that informed consent can be sought. Further visits/telephone contact can be arranged should the potential participant require more time before making a decision.

